### Study sample

We plan to include 352 individuals who are approached within 12 to 52 weeks after completing primary cancer treatment, independent of their primary cancer diagnosis. To be eligible to participate in the study, individuals must meet the criteria outlined in Table 1. Medical in- and exclusion criteria are checked by an involved physician at the treating hospital.

**Table 1 Tab1:** In- and exclusion criteria of the LION-RCT

**Inclusion criteria**	**Exclusion criteria**
• Age ≥ 18 years • Diagnosed with any type of invasive or hematological cancer • Completed primary cancer treatment with curative intent • Received systemic chemotherapy (or a stem cell transplantation in case of a hematological malignancy) as part of primary cancer treatment^a^ • For individuals undergoing endocrine, targeted, or immunotherapy, their maintenance treatment is not scheduled to be discontinued within the next 6 months • No evidence of distant metastatic disease (in case of solid tumors) • ECOG performance status ≤ 2 • Presence of at least one of the following side effects^b^: - Fatigue - Emotional distress - Perceived low physical functioning in daily life - Chemotherapy-induced peripheral neuropathy (CIPN) after having received neurotoxic chemotherapy • Access to stable internet connection • Able and willing to perform the exercise program and wear an activity tracker • Able to read, speak and understand the main country language	• Too physically active (i.e., > 150 min/week of moderate-to-vigorous intensity exercise) or participation in an exercise program comparable to the LION exercise program • Participated in a structured exercise intervention comparable to the LION exercise program during cancer treatment • Received chemotherapy for a previous cancer diagnosis within the past 5 years, or is experiencing ongoing side effects from previous chemotherapy regardless of when it was administered^c^ • Unable to complete the assessments or exercise sessions • Unstable on psychotropic medication^d^ • Any contraindications for exercise, including: - Severe neurologic or cardiac impairment according to ACSM criteria [17] - Uncontrolled severe respiratory insufficiency or dependence on oxygen suppletion in rest or during exercise - Uncontrolled pain • Any circumstances that would impede the ability to provide informed consent or adhere to the study requirements • Unable to attend the exercise program for more than 1 week

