**Fig. 1 Fig1:**
[figure not shown]
Recruitment and LION-RCT procedures

To be eligible for the study, potential participants have to score above the threshold (Table 2) for at least one of the targeted side effects. Individuals who do not score above the threshold for any of the side effects are provided with country-specific resources related to exercising following a cancer diagnosis. Individuals who score above the threshold for multiple side effects meet with a member from the local research team to identify their most burdensome side effect through a shared decision-making process. Following this process, eligible participants are invited for their baseline visit (i.e., assessment of anthropometrics and physical fitness/performance, and blood draw).

**Table 2 Tab2:** Pre-defined cut-off values for the side effects

**Side effect**	Questionnaire	Cut-off value
**Fatigue** [18]	EORTC QLQ-C30 fatigue symptom scale	> 39
**Emotional distress** [19]	PHQ-ADS	≥ 20
**Physical function** [18]	EORTC QLQ-C30 physical function scale	< 83
**CIPN**^**a**^** [**20]	PRO-CTCAE^b^	> 0

^a^Participants need to have been exposed to neurotoxic chemotherapy

^**b**^This questionnaire is used for eligibility screening only

After the baseline visit, participants are randomly allocated (1:1) to either the intervention or wait list control group by central computerized randomization using a blocked computer-generated sequence, effectively concealing the random allocation sequence. Castor EDC®, a cloud-based clinical data management platform, is used for randomization and data capture. Randomization is stratified by the participant’s most burdensome side effect, country and sex. Due to the nature of the intervention, blinding of participants and the study team to intervention assignment is not possible. However, data analysts will remain blinded to group allocation until the primary analyses have been completed. Participants randomized to the intervention group receive exercise instructions and an exercise kit at the end of their baseline visit. This kit includes the necessary exercise equipment to set-up their home exercise space: gym mat, dumbbell set with adjustable weights, resistance bands and an aerobic stepper. The wait list control group receives this kit 12 weeks post-baseline. All participants receive an activity tracker (Fitbit) at baseline.

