### Sample size

The sample size is based on the expected minimal improvement of either or both primary outcomes, i.e., HRQoL or the participant’s most burdensome side effect, from baseline to 12 weeks post-baseline relative to wait list control. To adjust for multiple testing, the Bonferroni-Holm method will be used. A Cochrane meta-analysis on RCTs with exercise interventions in breast cancer survivors after adjuvant chemo- and/or radiotherapy reported an effect size (95% CI) of 0.39 (0.21–0.57) for HRQoL and 0.34 (0.05–0.62) for depression, 0.33 (0.18–0.49) for perceived physical function, and 0.32 (0.18–0.47) for fatigue [43]. The subgroup of studies with combined aerobic and resistance exercises showed a higher effect size of 0.63 (0.08–1.19) for HRQoL and 0.47 (0.02–0.92) for fatigue. A meta-analysis comprising patients with mixed cancer entities after end of treatment also showed an effect size of 0.47 (0.29–0.65) for combined exercise on fatigue [44]. Further, higher effects are typically reached in studies enrolling only patients with the targeted symptom or side effect as well as with supervised compared to unsupervised exercise interventions [9, 11]. Hence, our planned intervention is expected to have effects that are in the higher range of previously reported studies. We performed a simulation study to calculate the power of the study considering that two primary outcomes will be tested and that a meta-analytic procedure will be used to obtain an average standardized effect size for participant’s most burdensome side effects. We assumed an effect size of 0.35 to obtain a conservative estimate for the required sample size. In the simulations, we assumed a correlation of 0.3 between the two primary outcomes. In case of a common effect size of 0.35 for HRQoL and participant’s most burdensome side effects in all four strata, a sample size of 280 individuals living beyond primary curative cancer treatment (*n* = 140 per study group) was found to yield 80% power to detect an effect on each individual primary outcome, with an overall alpha of 0.05. To account for a potential drop-out of around 20%, a total number of 352 individuals will be enrolled (*n* = 176 per study group). This sample size will also facilitate exploratory moderator and subgroup analyses to better understand which individuals benefit most from exercise.

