#### Statistical analysis

Descriptive statistics will be used to characterize the study population at baseline. Questionnaire scores will be calculated according to published scoring manuals. All analyses will be performed according to the intention-to-treat principle, including all randomized participants in the groups to which they were assigned, irrespective of adherence.

A positive result at the 12-week assessment of any of the two primary outcomes (i.e., HRQoL and the participant’s most burdensome side effect) is of main interest. Statistical testing for the intervention effect will be done separately for each primary outcome. HRQoL will be assessed using the EORTC QLQ-C30 summary score. For the participant’s most burdensome side effect, a meta-analytic procedure will be used to obtain an average standardized effect size (ES) (see below for further details). To adjust for multiple testing, the Bonferroni-Holm method will be used to maintain an overall alpha level of 5%. Two-sided 95% confidence intervals for the effect estimates for both primary outcomes will be presented.

A mixed model for repeated measures will be used to assess the intervention effect on the primary outcome HRQoL, while taking the hierarchical structure of the data into account (participants nested within countries). Models will be adjusted for the baseline value of the outcome and stratification factors (i.e., sex, country and the participant’s most burdensome side effect) and will include participants for whom the outcome is observed at two or more timepoints. Time since completion of curative treatment will be added as a cofactor, if there is an imbalance between groups. The primary contrast will be the comparison of the mean outcomes at 12 weeks between the intervention and control group adjusted for the baseline value.

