This is an international study, which is conducted across geographically and culturally diverse countries in Northern, Central, and Southern Europe, and in Australia. These regions vary in terms of physical exercise promotion and support for cancer survivors. As such, this study is well-positioned to enhance external validity and support broader generalizability of the findings across different healthcare contexts.

To allow for initial natural recovery, only individuals who completed their curative treatment at least 3 months ago are eligible for study participation. Further, they need to be recruited within 1 year of completing their primary treatment, since side effects that persist longer than 1 year may have established chronically and require more complex multidisciplinary treatment.

Over the past decade, exercise-oncology trials have provided strong evidence supporting the beneficial effects of supervised exercise on HRQoL, fatigue, anxiety and depressive symptoms and low perceived physical functioning. For these outcomes, the American College of Sports Medicine (ACSM) published exercise recommendations in terms of frequency, intensity, time and type of training (FITT criteria) to individualize exercise prescription [7]. These recommendations have formed the basis of our live-remote exercise program. The four specific modules were chosen based on the most common side effects of cancer and its treatment. Apart from CIPN, sufficient evidence shows that these side effects can be addressed through exercise. CIPN was included because emerging evidence suggests that exercise, particularly sensorimotor training, may help reduce CIPN [24].

HRQoL and the participant’s most burdensome side effect are analyzed as separate co-primary outcomes. However, some conceptual overlap may exist between them. For instance, the HRQoL summary score also includes a component on fatigue, one of the potential most burdensome side effects, although with less detail than the chosen outcome measure for fatigue for the co-primary analyses. Nevertheless, by analyzing both outcomes separately and applying appropriate correction for multiple testing, we aim to assess the effect of a live-remote exercise program on both HRQoL as well as on the side effect that each participant considers most burdensome.

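### Time since treatment enters the HRQoL primary model only if the groups look imbalanced; its inclusion should be fixed in advance

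*Protocol article*

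**What the plan says.** The Statistical analysis section of the protocol article sets out a mixed model for repeated measures for HRQoL, one of the two primary outcomes. Part of the covariate set is unconditional: "Models will be adjusted for the baseline value of the outcome and stratification factors", the factors being sex, country and most burdensome side effect. One further covariate is conditional: "Time since completion of curative treatment will be added as a cofactor, if there is an imbalance between groups". The same section applies the HRQoL analysis to secondary outcomes assessed at more than two time points. Nothing elsewhere in the article makes the covariate unconditional.

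Three other places bear on this:

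- **Recruitment and randomization:** "Randomization is stratified by the participant’s most burdensome side effect, country and sex". Time since treatment is not among the stratification factors. The same section says that "data analysts will remain blinded to group allocation until the primary analyses have been completed".
- **Study sample:** participants are "approached within 12 to 52 weeks after completing primary cancer treatment", so the variable has a wide range.
- **Discussion:** the lower limit is explained by "To allow for initial natural recovery, only individuals who completed their curative treatment at least 3 months ago are eligible for study participation", and the upper limit by the view that "side effects that persist longer than 1 year may have established chronically".

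**The concern.** The allocation sequence is concealed and not stratified on time since treatment, so any difference between the groups on it arises by chance. The size of that difference says nothing about whether the variable predicts HRQoL at 12 weeks, which is the reason to adjust for it.

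Conditioning on observed balance has two consequences. First, the confirmatory model is not settled until baseline data have been compared by group. A threshold set in the analysis plan would make the choice reproducible, but the data would still make it. Second, if the variable is prognostic, its precision gain is lost in every trial where the groups look balanced, which is most of them.

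**Working it through.** **Inputs from the protocol article (Sample size; Statistical analysis).** 140 evaluable per group, standardized effect 0.35, correlation 0.3 between the two primary outcomes, Bonferroni-Holm at overall alpha 0.05, drop-out around 20%, 352 enrolled.

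**Assumptions, because the article gives no figure.**

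- Partial correlation rho between time since treatment and the 12-week outcome, given the covariates already in the model: 0 to 0.4.
- Imbalance criterion: p<0.05, p<0.10, or absolute standardized mean difference (SMD) above 0.1.
- Two-sided tests.
- A single 12-week comparison stands in for the repeated-measures model.

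**Step 1: reproduce the plan's power.** The standard error of the standardized difference is √(2/140) = 0.1195, and 0.35/0.1195 = 2.928.

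- At alpha 0.05: Φ(2.928 − 1.960) = Φ(0.968) = 83.4%.
- At alpha 0.025, the first Holm step: Φ(2.928 − 2.241) = Φ(0.687) = 75.4%.
- Full Holm procedure on two normal statistics with correlation 0.3 (2 million draws): 80.8% per outcome, against 80% stated.
- Drop-out: 280/0.80 = 350, against 352 stated.

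The plan's figures reproduce without this covariate.

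**Step 2: how often the covariate would enter.** Under randomization its SMD is approximately normal with standard deviation 0.1195. A p<0.05 criterion admits it in 5% of trials and p<0.10 in 10%. For SMD above 0.1: 0.1/0.1195 = 0.837, and 2 × (1 − Φ(0.837)) = 40%. It is therefore left out in about 95%, 90% or 60% of trials.

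**Step 3: what always adjusting is worth.** The standard error becomes 0.1195 × √(1 − rho²). At rho 0.3 this is 0.1195 × 0.954 = 0.1140, and power at the first Holm step is Φ(0.35/0.1140 − 2.241) = Φ(0.829) = 79.6%.

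**Step 4: simulate the rule.** 140 per group, tested at 0.025, with 100,000 runs under the effect of 0.35 and 200,000 under the null for each scenario. Ranges run over the three imbalance criteria.

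| rho | Power, always adjusted | Power, conditional rule | Gain (points) | Type I error of the rule (nominal 0.025) |
|---|---|---|---|---|
| 0 | 74.7–74.9% | 74.7–75.0% | about −0.1 to 0 | 0.024–0.025 |
| 0.1 | 74.9–75.4% | 74.6–75.2% | 0.2–0.3 | 0.025 |
| 0.2 | 76.5–76.8% | 75.2–75.6% | 0.9–1.5 | 0.023–0.024 |
| 0.3 | 78.9–79.2% | 75.2–77.0% | 2.0–3.7 | 0.022–0.023 |
| 0.4 | 82.2–82.7% | 75.8–78.8% | 3.7–6.9 | 0.020–0.022 |

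Gains are taken within the same set of runs. Allowing for simulation error, the gain at rho 0.1 is best read as 0 to 0.4 points. At rho 0.3 the standard deviation of the effect estimate is about 0.115 to 0.118 under the rule and 0.114 when the covariate is always included.

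**Why the rule is conservative.** When the covariate is left out, the trial has been selected for near-balance on it. The estimate then varies less than the model's standard error allows, because that standard error still carries the unexplained variation.

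**The case against.** The strongest reply is that the trigger is a baseline comparison, not an outcome result, and that analysts are blinded until the primary analyses are complete. That stands. A reader might infer that having two candidate models inflates the type I error. For a single test at 5%, reporting the smaller of the two p-values would give 6.1%, 6.5% and 6.9% at correlations of 0.2, 0.3 and 0.4. The article permits no such choice, however, and blinding makes it less likely. Simulated as written, the rule is slightly conservative.

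Three further objections also stand in part:

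- **Prognostic value is not asserted.** The Discussion passages justify the eligibility window; they do not say that time since treatment predicts the 12-week outcome within it. Baseline adjustment may absorb part of any association. The grounds are indirect and come without a figure, which is why a range is shown. At rho 0.1 or below, almost nothing is lost.
- **The missing threshold is not a fault of the article.** The analysis plan sits in the IRB protocol, which is not at hand, and may define imbalance. The criticism is of the conditional principle, which a threshold would not cure.
- **The rule is not stated for the side-effect endpoint.** It stands in the HRQoL paragraph. The description of the pooled standardized effects neither adopts nor excludes it.

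**Conclusion.** The point holds as one of precision and pre-specification. A covariate of the confirmatory HRQoL model, and of the secondary models that copy it, is selected on chance imbalance and would usually be omitted: in about 60% to 95% of trials under the criteria tried. The loss relative to always adjusting ranges from negligible at a partial correlation of 0.1 to about 4 to 7 points of power at 0.4, at the first Holm step. These figures rest on the assumed correlations and imbalance criteria and on a simplified single-time-point model.

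The documents do not support a claim of inflated type I error or of an underpowered trial: the stated 80% power reproduces without the covariate and the planned sample size is unaffected. The change is worth making because it costs almost nothing and leaves one primary model, fixed in advance.

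**What to change.** Delete the condition. State in the protocol and analysis plan, before unblinding, that time since completion of treatment is always included in the HRQoL model and in the secondary models that copy it, whatever the observed balance. Fix its form in advance, for example continuous weeks; the form is the trial team's choice, since early recovery and later chronicity need not imply a straight line. Report the model without it as a sensitivity analysis only. Including the same covariate in the stratum-specific side-effect models is an optional extension.

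The cost is one sentence and one degree of freedom for a linear term. If the variable proves unrelated to outcome, the simulated loss of power is about 0.1 point. The sample size does not change.

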### Cost-utility analysis

In the cost-effectiveness evaluation, the net costs and effects incurred with both strategies (live-remote exercise program vs wait list control) will be compared at 12 weeks post-baseline (i.e., primary time point). The results of both cost and effect measurements will be integrated using cost-utility analyses. The analysis will be performed from a societal perspective with a time horizon of 12 weeks. Because of the short time horizon, discounting is considered redundant. In the cost-utility analysis, efficiency is expressed in terms of costs per QALY. Incremental costs and incremental effects, expressed in a ratio will be estimated. A probabilistic uncertainty analysis using bootstrapping will be performed. As it is unlikely that the full pay-back period of investments of live-remote training will be visible after a follow-up of 12 weeks, we will extrapolate findings of the economic evaluation alongside in a model-based study and determine the potential cost-effectiveness at 36 weeks and a lifetime time horizon. For this model-based study, we will combine the trial data with literature data and expert opinion scenarios.

### Analysis of live-remote testing

Agreement between live-remote and in-person tests will be determined with a Bland and Altman analysis and by using intraclass correlations (ICC) two-way mixed-effects models with absolute agreement since each measurement from the participant will be rated by the same assessor. Interpretations of the ICCs will be based on Koo and Li’s guidelines [45]: ICC values < 0.5 = poor reliability; 0.5–0.75 = moderate reliability; 0.75–0.9 = good reliability; and > 0.9 = excellent reliability.

### Analysis of the sensor-based sub-study

Feasibility outcomes related to usability and experience scores will be presented as mean ± SD along with 95% confidence intervals. Qualitative data collected from semi-structured interviews with participants and exercise professionals will be analyzed using thematic analysis to explore their subjective experiences, perceptions of usability, and detailed feedback regarding the feasibility of the technology and sensor-based exercise guidance.

### Concept mapping analysis

Statements generated and ranked by participants will be further analyzed using cluster analysis. This results in a visual map of related aspects, aggregated at a group level. This so-called “point-cluster” map is then used to identify and name overarching concepts. For each overarching concept, researchers will translate statements into actionable features and rank these according to importance and feasibility. This results in a “Go-zone map” per focus area of interest (i.e., group interaction and patient-trainer interaction), identifying which features are both feasible and important to pursue for optimizing delivery of the live-remote exercise intervention in future implementation.

## Discussion

In the current trial, we are investigating the (cost-)effectiveness of side effect-targeted, live-remote exercise for individuals living beyond primary curative cancer treatment on HRQoL and the participants’ most burdensome side effects. What makes this trial innovative is its use of live-remote exercise delivery, allowing real-time personalized support and feedback regardless of geographic location. The trial targets patients in need of (exercise) support. Our exercise program targets the participant’s most burdensome side effect, ensuring that the intervention is tailored to each participant’s specific needs, which better reflects clinical practice compared to a uniform exercise program.

We set out to address this aim through an international, multicenter RCT with a super umbrella design, i.e., combining a basket trial (i.e., participants with different side effects are all receiving the same exercise main module) with an umbrella trial (i.e., participants receive additional exercise modules targeted to their most burdensome side effect irrespective of cancer type). We chose to conduct a superiority trial rather than a non-inferiority trial with an in-person supervised exercise program as the comparator, as the latter would significantly reduce feasibility due to the large sample size required. Moreover, our aim is not to replace in-person supervised exercise programs. Instead, by comparing our live-remote exercise program to a control group, we aim to demonstrate that live-remote exercise can also be a suitable and effective option for individuals living beyond primary curative cancer treatment. Our control group is a wait list control group that receives the same live-remote exercise program after primary outcome assessment. A wait list control group was included for ethical reasons, since the current evidence suggests that all cancer survivors who experience side effects should have access to exercise support. In addition, it provides the unique opportunity to test the feasibility of remote physical fitness testing and remote sensor-based exercise guidance without compromising the validity of the RCT. We consider the additional wait time for the control group to be ethically sound, since meta-analyses have not found evidence that the timing of exercise interventions moderate their success [9–11].

This is an international study, which is conducted across geographically and culturally diverse countries in Northern, Central, and Southern Europe, and in Australia. These regions vary in terms of physical exercise promotion and support for cancer survivors. As such, this study is well-positioned to enhance external validity and support broader generalizability of the findings across different healthcare contexts.

To allow for initial natural recovery, only individuals who completed their curative treatment at least 3 months ago are eligible for study participation. Further, they need to be recruited within 1 year of completing their primary treatment, since side effects that persist longer than 1 year may have established chronically and require more complex multidisciplinary treatment.

Over the past decade, exercise-oncology trials have provided strong evidence supporting the beneficial effects of supervised exercise on HRQoL, fatigue, anxiety and depressive symptoms and low perceived physical functioning. For these outcomes, the American College of Sports Medicine (ACSM) published exercise recommendations in terms of frequency, intensity, time and type of training (FITT criteria) to individualize exercise prescription [7]. These recommendations have formed the basis of our live-remote exercise program. The four specific modules were chosen based on the most common side effects of cancer and its treatment. Apart from CIPN, sufficient evidence shows that these side effects can be addressed through exercise. CIPN was included because emerging evidence suggests that exercise, particularly sensorimotor training, may help reduce CIPN [24].

HRQoL and the participant’s most burdensome side effect are analyzed as separate co-primary outcomes. However, some conceptual overlap may exist between them. For instance, the HRQoL summary score also includes a component on fatigue, one of the potential most burdensome side effects, although with less detail than the chosen outcome measure for fatigue for the co-primary analyses. Nevertheless, by analyzing both outcomes separately and applying appropriate correction for multiple testing, we aim to assess the effect of a live-remote exercise program on both HRQoL as well as on the side effect that each participant considers most burdensome.

In exercise-oncology trials, exercise effects may be impacted by low adherence to the intervention and contamination in the control group. To improve attendance and compliance, our exercise sessions are tailored to individual needs, supervised by upskilled exercise professionals, and delivered live-remote via Zoom. This approach enables participants to join sessions from their homes or another location of their choice, minimizing barriers such as travel distance and time constraints that often hinder in-person attendance. Additionally, we closely monitor adherence and compliance in the study. Since it is impossible to blind participants in exercise-oncology trials to their respective study group, the risk of contamination is increased. To decrease this risk, we take several measures, i.e., we include relatively inactive cancer survivors and have a wait list control group. A systematic review showed that offering an exercise program after the intervention period is associated with less contamination and lower drop-out rates in the control group [46]. In addition, we clearly explain the randomization procedure to avoid disappointment when being randomized to the wait list control group and provide an activity tracker. Although providing the activity tracker may increase physical activity levels, research indicates that offering something to a control group helps to lower risk of contamination [46]. Additionally, the activity tracker will provide insight into the degree of contamination.

In summary, in the LION-RCT we examine the effects of a personalized, live-remote exercise program for individuals experiencing persistent side effects following cancer treatment and in need of supportive care. Exercise effects on HRQoL and the individual’s most burdensome side effect, as well as a range of other health outcomes will be assessed. If live-remote exercise after curative cancer treatment is proven to be (cost-)effective, implementing live-remote exercise in addition to in-person exercise would be a logical next step. This will improve the accessibility and health equity of exercise-based supportive care strategies for all cancer survivors, including those living in rural and remote areas. The results of our study can inform delivery of live-remote training and testing, which is of relevance for clinical practice and future studies. Furthermore, it can also inform international guidelines with respect to the role of live-remote exercise in improving HRQoL and reducing cancer- and treatment-related side effects in cancer survivors.

